### Interim analyses {21b}

No interim analysis of the primary outcome is planned, owing to the small sample size. However, given the severity of the disease of enrolled patients, we plan an interim safety analysis of the mortality rate at 72 h of inclusion in both study groups, after the enrollment of the first 20 patients.

### Methods for additional analyses (e.g., subgroup analyses) {20b}

Exploratory subgroup analyses regarding the primary outcome will be performed by comparing both arms of the study in the following subgroups of patients:Diagnosis of septic shock at the time of inclusion [28]SOFA score at inclusion strictly greater (>) or lower (≤) than the median value of enrolled participants [17]Fluid overload strictly greater (>) or lower (≤) than 10% of admission body weight at inclusion, as per the stratification [2]Cardiac index at inclusion strictly greater (>) or lower (≤) than 2.5 l min^−1^ m^−2^Arterial lactate concentration at inclusion strictly greater (>) or lower (≤) than 2 mmol l^−1^Preload dependence status (dependent or independent) at inclusion, identified by the postural maneuverVasopressor dose at inclusion strictly greater (>) or lower (≤) than the median value of enrolled participantsPaO_2_ to FiO_2_ ratio at inclusion greater (≥) or strictly lower (<) than the median value of enrolled participants

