### Sample size {14}

We make the hypothesis that the fluid balance will be of 4000 ± 4000 ml at H72 of inclusion in the control group and that the intervention strategy will generate a fluid balance of 0 ± 4000 ml at H72 of inclusion (absolute between groups difference of 4000 ml). The hypothesis is based on the data reported by a large randomized controlled trial evaluating the timing of RRT in the ICU, in which the H72 cumulative fluid balance was 3711 ml in the early arm and 3917 ml in the delayed arm of the study [18]. Based on this hypothesis, the required sample size to compare two means between two equally sized samples (and a bilateral hypothesis), with a *⍺* of 0.05 and a power 1–*β* of 0.8, would be 16 patients per arm, hence a total of 32 patients. Since (1) we expect a non-survival rate of 25% at 72 h of inclusion (corresponding to the time point of the primary outcome evaluation) and (2) the expected distribution of the primary outcome would not follow the normal distribution, justifying an increase of 25% in sample size, the final total number of patients to enroll would be 58, equally distributed between study groups. Patients deceased before 72 h of inclusion, or alive at H72 but with a missing primary outcome measure, will not be included in the analysis of the primary outcome. Once the required number of 21 patients per arm with an assessable primary outcome will be reached, inclusions will cease.

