## Statistical methods

### Statistical methods for primary and secondary outcomes {20a}

#### General comments and descriptive analysis

All analyses will be performed using the R software for statistical computing (R Core Team). A *p* value < 0.05 will be considered significant.

Patients’ characteristics at enrollment will be reported in each study group to help evaluate allocation balance. Continuous variables will be reported using median and interquartile range (with minimum and maximum values) and compared between the groups using the Mann-Whitney test. Categorical variables will be reported using count and percentage (including missing values) and compared between the groups using the chi-squared test or Fisher exact test, as appropriate. Missing value count and percentage of each reported variable will be given.

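### The exploratory subgroup analyses compare the arms separately within the levels of eight factors, which does not test whether the effect differs between levels

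*Protocol article*

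**What the plan says.** The section on additional analyses {20b} states the method: "Exploratory subgroup analyses regarding the primary outcome will be performed by comparing both arms of the study in the following subgroups of patients". Eight baseline factors follow. Seven are given with both levels. The first, "Diagnosis of septic shock at the time of inclusion", is given as a diagnosis only. So 15 levels are listed, or 16 if absence of septic shock is counted.

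Three factors are split at the median, for example "SOFA score at inclusion strictly greater (>) or lower (≤) than the median value of enrolled participants"; the other two are vasopressor dose and the PaO2/FiO2 ratio. The remaining five use a diagnosis, a fixed cut-off or preload status.

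The section names neither a test nor a rule for reading a difference between levels. The general comments on the statistical methods set one threshold and exempt no analysis: "A *p* value < 0.05 will be considered significant". The primary outcome is compared by the Mann-Whitney test (Primary outcome analysis). An interaction term does appear in the plan, but only group by time for the longitudinal secondary outcomes (Analysis of the secondary outcomes).

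**The concern.** Several of the listed factors (preload dependence, cardiac index, lactate) are also inputs to the hemodynamic protocol of the intervention arm. The natural question about them is whether the intervention works differently in different patients. A separate comparison in each level cannot answer it. One level can reach p < 0.05 and the other miss it when the true effect is identical in both, simply because each level holds only part of an already small sample.

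The Discussion says the trial should help design a larger trial and help refine or simplify the hemodynamic protocol. It does not say that subgroup results will drive those decisions. If they were used that way, chance patterns could point them in the wrong direction.

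**Working it through.** **Inputs from the Sample size section.** The "absolute between groups difference of 4000 ml" with SD 4000 ml in each arm gives a standardised effect of 1.0. The test is two-sided ("and a bilateral hypothesis") at 0.05, with "a power 1–*β* of 0.8". Inclusions stop at 21 evaluable patients per arm.

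**The plan's own figure.** n per arm = 2 × (1.960 + 0.842)² × (4000/4000)² = 15.7, rounded up to 16, as stated. Allowing for 25% deaths, 16/0.75 = 21.3, which matches the stopping number of 21.

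**Assumptions, not in the documents.** The Mann-Whitney test carries over to the subgroups. The outcome is normal. The prevalence of a factor level is 30–70%. The latent correlation between factors is 0–0.5. The true effect is the same in every patient, so any apparent difference between levels is false.

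**Power, normal formula:** Φ(√(n/2) − 1.96).
- Whole trial, n = 21: Φ(3.24 − 1.96) = 90%. Mann-Whitney by simulation gives about 87%.
- Even split, n ≈ 10.5 per arm: Φ(2.29 − 1.96) = 63%. Mann-Whitney gives 53–57%.
- 70/30 split, about 15 and 6 per arm: Mann-Whitney gives 71% and 30%.

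**Chance that one factor is significant in one level only:** p₁(1 − p₂) + p₂(1 − p₁).
- Even split: 0.53 × 0.43 + 0.57 × 0.47 = 0.50. Two sets of simulations give 49% and 51%.
- 70/30 split: 0.71 × 0.70 + 0.30 × 0.29 = 0.58. Simulations give 58% and 60%.
- The normal formula gives 47% and 54%. A more extreme split (17 and 4 per arm) gives 71% by simulation.

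**Chance of at least one such factor among eight.** This was simulated because all factors share the same 42 outcomes. The grid used an exact two-sided Mann-Whitney test, 2,500 runs per setting, and the ranges above for prevalence and correlation.

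| True common effect | Mean number of discordant factors | At least one of eight |
|---|---|---|
| 5400 ml | 2.8–3.7 | 74–93% |
| 4000 ml | 4.0–4.5 | 88–95% |
| 3000 ml | 3.5–3.8 | 83–87% |
| 2000 ml | 2.2–2.3 | 65–67% |
| 0 ml | 0.6–0.7 | 31–35% |

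A second, separate simulation gave 88–97% at 4000 ml, about 69% at 2000 ml and 30–35% at zero.

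**The alternative, one arm-by-subgroup interaction test per factor (linear model, same simulated data).** The false-signal rate is about 5% per factor whatever the common effect. At least one of eight is falsely significant in 28–35% of trials; with independent tests it would be 1 − 0.95⁸ = 34%. For an even split, the SE of the interaction is 4000 × √(4/10.5) ≈ 2470 ml. Power for a 4000 ml interaction is Φ(4000/2470 − 1.96) = Φ(−0.34) ≈ 37%. The interaction detectable with 80% power is 2.80 × 2470 ≈ 6900 ml.

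**The case against.** The analyses are called exploratory, are confined to the primary outcome, and carry no rule for declaring a subgroup effect. A reader might infer that subgroup effects will be judged by within-level significance. The text does not say so: the 0.05 threshold is a general statement, and reading significant-here-but-not-there as effect modification is an error of interpretation to which the plan does not commit itself. That stands, and it limits the point to a risk that the stated method leaves open.

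The SAP and the full protocol are not shown and could add an interaction estimate. That also stands, so the absence of a named interaction test is not the complaint. The complaint is about the method the article does state, and an added test would not make the within-level comparisons answer the question.

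The arithmetic needs limits as well. About 10–11 patients per arm follows only for the three median splits, because the documents give no prevalence for the other five factors. The Mann-Whitney test in subgroups is an assumption.

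Finally, interaction tests do not rescue the subgroups. With no treatment effect, eight unadjusted interaction tests raise a false signal about as often as the within-level comparisons produce a discordant factor. The gain appears when a common effect exists: about 5% per factor instead of about 50–60%.

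**Conclusion.** The point holds as a weakness of the stated method. Within-level comparisons in a trial of 42 evaluable patients do not test differences between levels. If the trial succeeds as planned, about half of the factors would look discordant by chance alone. At the planning effect the rate is about 50–60% per factor and about 88–97% for at least one of eight.

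A reader might infer that false patterns appear almost always. The figures support that only for at least one factor out of eight, and only near the planned 4000 ml effect. The chance is about 65–70% at 2000 ml and about 30–35% with no effect.

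These sizes rest on the Mann-Whitney test being reused, 21 evaluable patients per arm, a normal outcome, a uniform true effect, and the assumed ranges of prevalence and correlation. Neither the present method nor its replacement makes the subgroups informative at this sample size. The replacement shows the uncertainty where discordant p values would hide it.

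**What to change.** In the section on additional analyses:
- For each of the eight factors, report an arm-by-subgroup interaction estimate with 95% CI, from a linear or rank-based model on fluid balance at H72.
- Show within-level differences as estimates with CIs and without p values.
- State that no subgroup claim will rest on significance within a level.
- Keep the exploratory label, and add that power for interaction is low, that the eight interaction tests are not adjusted for multiplicity, and that the results are likely to be inconclusive.

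The cost is a change of wording and eight model fits, with no new data. The downside is wide intervals, and at least one false interaction signal in about 28–35% of trials if unadjusted p values are read at 0.05. For that reason the estimates and intervals should carry the message.

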### Methods in analysis to handle protocol non-adherence and any statistical methods to handle missing data {20c}

The ITT population will consist of all enrolled patients, fulfilling eligibility criteria (inclusion and exclusion), analyzed as per their allocation group, regardless of their adherence to the protocol and the UF_NET_ rates they received, and followed until day 90 after inclusion, loss to follow-up, or death, whichever comes first. All secondary outcomes will be analyzed in the ITT population.

The modified ITT is a subset of the ITT population comprising all patients alive at 72 h of inclusion, fulfilling eligibility criteria (inclusion and exclusion), analyzed as per their allocation group, regardless of their adherence to the protocol and the UF_NET_ rates they received, and followed until day 90 after inclusion, loss to follow-up, or death, whichever comes first. This population hence will not include patients who died before H72 or those who ceased trial participation before H72. The primary outcome will be analyzed in the modified ITT population.

The rate of missing data per variable will be reported. No imputation of missing data is planned, and missing data will not be replaced.

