**Methods:**

The GO NEUTRAL trial is a multicenter, open-labeled, randomized, controlled, superiority trial with parallel groups and balanced randomization with a 1:1 ratio. The trial will enroll adult patients with acute circulatory failure treated with vasopressors and severe acute kidney injury requiring CRRT who already have been equipped with a continuous cardiac output monitoring device. After informed consent, patients will be randomized into two groups. The control group will receive protocolized fluid removal with an UF_NET_ rate set to 0–25 ml h^−1^ between inclusion and H72 of inclusion. The intervention group will be treated with an UF_NET_ rate set on the CRRT of at least 100 ml h^−1^ between inclusion and H72 of inclusion if hemodynamically tolerated based on a protocolized hemodynamic protocol aiming to adjust UF_NET_ based on cardiac output, arterial lactate concentration, and preload dependence assessment by postural maneuvers, performed regularly during nursing rounds, and in case of a hemodynamic instability episode. The primary outcome of the study will be the cumulative fluid balance between inclusion and H72 of inclusion. Randomization will be generated using random block sizes and stratified based on fluid overload status at inclusion. The main outcome will be analyzed in the modified intention-to-treat population, defined as all alive patients at H72 of inclusion, based on their initial allocation group.

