### Criteria for discontinuing or modifying allocated interventions {11b}

Changes in UF_NET_ based on hemodynamic and/or respiratory evaluations as per each study group are described above.

Temporary contra-indications to the study procedures are:Transient suspension of RRT for less than 8 h due to patient transfer to the operating room or the imaging facilityOccurrence of active hemorrhage requiring blood transfusion and whose resolution is expected in less than 8 hTransient contra-indication to a postural maneuver to assess preload dependence, such as lower limb immobilization or abdominal compartment syndrome, if they last less than 8 h

Permanent contra-indications to study procedures are:Consent removal or refuse to participate after an inclusion following the emergent procedurePermanent suspension of RRT for more than 8 h, whatever the reasonAcute ischemic or hemorrhagic stroke complicated with coma and requiring mechanical ventilationOccurrence of active hemorrhage requiring blood transfusion and whose resolution is not expected in less than 8 hPermanent contra-indication to a postural maneuver to assess preload dependence, such as lower limb amputation or abdominal compartment syndrome, if they last more than 8 hContinuous cardiac output monitoring is no longer feasible due to irreversible technical issuesTransfer to a non-participating ICU

Patients could be withdrawn from the study at their request or the request of their legal representative, and their data will not be analyzed. In case of harm related to the study procedures identified as such by the treating clinician, patients will be managed outside the protocol, but will be left in their allocated study arm.

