### Outcomes {12}

#### Primary outcome

The primary outcome is the cumulative fluid balance measured between inclusion and 72 h after inclusion in alive patients at H72, computed as the difference between fluid input and output, quantified in milliliters over the same period. The primary outcome will be assessed in the modified intention-to-treat (ITT) population (see below for the definition of study populations).

Fluid input will be defined as any intravenous (either intermittently or continuously administered) or orally administered drugs or electrolytes diluted into a volume, enteral or parenteral nutrition, fluid bolus therapy, intravenous maintenance hydration, or blood products. Fluid output will comprise urine output, UF_NET_, and surgical drain output. Hence, some unquantifiable input or output will not be measured such as subcutaneous injections, perspiration, or stool volume. The input and output volumes composite of the primary outcome will be collected during nursing rounds as part of routine care.

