### Plans to promote participant retention and complete follow-up {18b}

Incomplete follow-up during ICU stay is not expected, given the studied population. Given that most outcomes (hemodynamic and physiologic monitoring, CRRT settings including UF_NET_, vasopressor, and mechanical ventilation and their weaning date) are specific to the ICU environment and stay of the participants, we do not expect missing values. Especially, input and output components of the primary outcome measure are reported every 4 h in the electronic ICU medical records and charts, either automatically or by the nursing staff at the bedside.

The procedure regarding the collection of the input and output components of the primary outcome and the procedure in case of missing values are detailed in SM3, Supplemental Table 3.

Missing values at day 28 or day 90 (vital status, day 90 creatinine, RRT weaning date) could occur for surviving patients after hospital discharge. Upon enrollment, patients’ and their next-of-kin contact information will be stored in the digital health record at each study site. Data regarding the vital status and RRT at day 28 or day 90 of inclusion will be retrieved following the ranked procedure described above.

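### The modified ITT definition excludes living patients under an undefined ceased-participation clause that conflicts with its own survival-only rule and with the Abstract

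*Protocol article*

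**What the plan says.** Section {20c} builds the modified ITT in two sentences. The first sets membership: "The modified ITT is a subset of the ITT population comprising all patients alive at 72 h of inclusion", subject to the eligibility criteria and analysed by allocated group "regardless of their adherence to the protocol and the UF_NET_ rates they received". The next adds: "This population hence will not include patients who died before H72 or those who ceased trial participation before H72".

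The other statements of the population carry no such clause. The Abstract (Methods) has it "defined as all alive patients at H72 of inclusion, based on their initial allocation group". The primary outcome in section {12} is the "cumulative fluid balance measured between inclusion and 72 h after inclusion in alive patients at H72".

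Two further rules bear on who is counted. Section {11b} says: "Patients could be withdrawn from the study at their request or the request of their legal representative, and their data will not be analyzed". Section {14} also leaves out patients "alive at H72 but with a missing primary outcome measure, will not be included in the analysis of the primary outcome", and section {20c} plans no imputation.

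On data availability, section {18b} says that the "input and output components of the primary outcome measure are reported every 4 h in the electronic ICU medical records and charts", and that missing values are not expected.

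**The concern.** Two analysts working from this text could build different primary populations. One would keep every eligible patient alive at H72. The other would also remove living patients judged to have left the trial. The protocol does not say what leaving means.

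The nearest candidate list is in section {11b}, under permanent contra-indications to study procedures. It puts consent removal beside RRT suspended for more than 8 h, stroke with coma, haemorrhage needing transfusion, a lasting contra-indication to the postural manoeuvre, failed cardiac output monitoring, and transfer to a non-participating ICU. If the clause reaches that list, patients are dropped because of events after randomisation, some of which directly affect fluid balance: suspending RRT ends net ultrafiltration, and blood products count as fluid input. The preceding sentence of section {20c} says adherence is irrelevant, so the population would no longer match its own description.

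The stops could also be unequal between arms. Treatment is open-label, and the algorithm with a manoeuvre every 4 h applies only to the intervention arm (section {11a}).

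**Working it through.** **1. The statements side by side**

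| Place | Alive at H72 required | Ceased-participation clause |
|---|---|---|
| Abstract, Methods | yes | no |
| Section {12}, primary outcome | yes | no |
| Section {20c}, defining sentence | yes, regardless of adherence | no |
| Section {20c}, following sentence | yes | yes, term undefined |
| Section {14} | yes, and outcome not missing | no |

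The clause is introduced as a consequence of the definition. Exclusion of the dead does follow from it. Exclusion of living patients does not.

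**2. Two readings of the clause**

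- *Consent only.* The clause repeats the section {11b} rule that withdrawn patients' data are not analysed. It then has nothing to do with adherence, and only the wording needs correcting.
- *All permanent contra-indications.* The clause removes living patients for non-adherence. One feature of the text favours this reading: the clause is written for the modified ITT only, whereas withdrawn consent would remove a patient from every population.

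**3. The plan's sample size, for scale** (section {14}: difference 4000 ml, SD 4000 ml, two-sided 0.05, power 0.80)

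- n per arm = 2 × (1.960 + 0.842)² × (4000/4000)² = 15.7, so 16 per arm and 32 in total. This matches.
- 32/0.75 = 42.7, rounded up to 43; 43/0.75 = 57.3, rounded up to 58. This matches. 16/0.75 = 21.3, consistent with 21 assessable per arm.
- The attrition allowance is for deaths only. Expected assessable patients if all survivors are kept: 58 × 0.75 = 43.5, against 42 needed.
- If 5%, 10% or 15% of enrolled patients cease participation alive (assumed; no rate is given): 58 × 0.70 = 40.6, 58 × 0.65 = 37.7, 58 × 0.60 = 34.8. Reaching 42 then needs 42/0.70 = 60, 42/0.65 = 64.6 (65), or 42/0.60 = 70 enrolled.

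**4. Worst-case selection** (assumed: 21 survivors per arm, normal data, SD 4000 ml, no true difference, the k highest balances removed from one arm only)

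The expected top three of 21 standard normal values are 1.889, 1.434 and 1.160. The shift in the mean difference is their sum over the k removed × 4000/(21 − k):

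- k = 1: 1.889 × 4000/20 = 378 ml
- k = 2: 3.323 × 4000/19 = 700 ml
- k = 3: 4.483 × 4000/18 = 996 ml

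Simulation of the same set-up agrees (about 370, 700 and 980 ml). It gives a two-sided Mann-Whitney type I error of about 6%, 8–9% and 12–13%, against 5% with nobody removed. With a true difference of 4000 ml, the estimated mean difference becomes about 4.4, 4.7 and 5.0 l.

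Section {20a} reports medians, which move less. For k = 2 the arm median drops from the 11th to the 10th of 21 ordered values, about 0.118 × 4000 = 472 ml.

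Exclusions unrelated to outcome cause no bias, only loss of patients.

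**The case against.** The best case against is that the clause means only consent. Elsewhere the article mostly uses participation for consent or follow-up (sections {26a} and {31a}, and the day 28 objectives). Section {11b} keeps patients harmed by study procedures in their allocated arm although they are managed off protocol, so stopping procedures is not automatically leaving the trial. This stands as an available reading. It does not remove the conflict with the Abstract and the defining sentence, and nothing in the text settles the matter.

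A reader might infer more than the document supports in four ways.

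- *That every permanent contra-indication removes a patient from the primary analysis.* The text never equates the two.
- *That exclusions fall mainly on the intervention arm and flatter it.* The routine 4-hourly algorithm is specific to that arm, but the secondary outcomes in section {12} call for cardiac index, extravascular lung water and preload classification of instability episodes in both arms. RRT suspension, haemorrhage, stroke and transfer are listed without regard to arm. If high-balance control patients were dropped, the bias would run towards no effect.
- *That a particular bias in millilitres is expected.* No cessation rate is given, and the worst-case figures require selection of the most extreme patients.
- *That survivor restriction is a hidden flaw with no check.* It is disclosed in the Abstract and in sections {12} and {14}, and allowed for in the sample size. Secondary outcome #7 compares normalised balance to H72 or death in the ITT population, whose definition lacks the disputed clause. H72 mortality by arm is also reported.

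**Conclusion.** The contradiction is real on either reading: section {20c} excludes living patients under an undefined term after defining the population by survival alone, and the Abstract and section {12} do not contain that exclusion. It matters because it decides who enters the primary analysis of a trial that stops at 21 assessable patients per arm, and because the data for most of these patients would be in routine charts.

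Bias depends on the wider reading and on the exclusions being related to fluid balance. Differential exclusion is a risk and has not been shown; its direction and size cannot be derived from the document. The shift of about 0.4 to 1.0 l and the type I error of about 6–13% are upper illustrations, resting on one-sided removal of the 1 to 3 most extreme of 21 patients, normal data and the protocol's SD. The effect on the planned medians would be smaller. On the consent-only reading, a clarification of wording is all that is needed.

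**What to change.** In section {20c}, limit the second exclusion to refusal or withdrawal of consent. State that every other randomised, eligible patient alive at H72 is analysed in the allocated arm, and that charted fluid input and output are collected to H72 after study procedures stop. The collection rule is essential: without it, the same patients would leave through the missing-outcome rule in section {14}.

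Align the Abstract and sections {12}, {14} and {20c} to this one definition, and report all exclusions from the primary analysis by arm and reason. Secondary outcome #7 can be cited as the supporting analysis; its direction need not be a condition for the primary conclusion. Make the change before database lock.

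The cost is a wording change and routine chart extraction for a few more patients. The estimated effect may be slightly diluted by patients who stopped the strategy, and charts may be unobtainable after transfer to a non-participating ICU.
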